### Participant timeline {13}

In the emergency room, the patient and parent/guardian are first informed about the study through posters and the informational flyer provided by the attending physician (Fig. 1). The patients and parents/guardians will be further informed about the study by the investigator by phone a few days prior to the scheduled appointment in the plaster room. If they are interested in participating, they will be sent written patient information and consent forms. In the plaster room, the investigator will collect the signed consent forms. The patients are then enrolled in the study and will complete a short questionnaire. Afterwards, the patient will be randomised, and the equipment (finger pulse oximeter, VR goggles and headphones) is placed on the child. The patient will then receive the plaster treatment. Right after the plaster intervention, all the equipment is removed. Lastly, a short questionnaire will be conducted with the child and parent. This concludes the participation of the child in this study.

**Fig. 1 Fig1:**
[figure not shown]
Flowchart of the study

### Sample size {14}

The expected anxiety score (CFS) in the control group is on average 1.78 ± 1.40 [11]. For an intended improvement by 0.5 (i.e. to 1.28) on the Child Fear Scale, with a statistical power of 80% and an alpha of 0.05, a sample size of 123 participants is needed in each group. To anticipate a 10% dropout, we will include 135 children in each group.

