### Methods in analysis to handle protocol non-adherence and any statistical methods to handle missing data {20c}

We expect the number of withdrawals to be low because the intervention is not invasive and does not increase the risks of the standard procedure. Additionally, all the data will be collected during the visit in the plaster room; there is no follow-up, which will also minimise the missing data. A maximum dropout and/or missing data of 10% is anticipated. We will analyse the data according to the intention-to-treat principle. A complete case analysis will be used.

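### Minor: the 10% dropout allowance multiplies 123 by 1.10 instead of dividing by 0.90, so 135 per group keeps the required 123 only up to 8.9% loss

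*Protocol article*

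**What the plan says.** The Protocol article, Sample size {14}, takes a control-group Child Fear Scale mean of 1.78 with SD 1.40 and plans "For an intended improvement by 0.5 (i.e. to 1.28) on the Child Fear Scale", "with a statistical power of 80% and an alpha of 0.05". From these it concludes that "a sample size of 123 participants is needed in each group. To anticipate a 10% dropout, we will include 135 children in each group". The abstract carries this forward as a total of 270.

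The section on non-adherence and missing data {20c} gives the same percentage as an upper limit: "A maximum dropout and/or missing data of 10% is anticipated". It also settles what happens to children without an outcome: "A complete case analysis will be used".

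**The concern.** The only reason given for enrolling 135 rather than 123 is to absorb a 10% loss. If 135 less 10% is under 123, the allowance does not do what it is said to do. Nothing in the analysis offsets this, because a child without a post-procedural score drops out of the comparison. What is at stake is whether the stated combination of 123 evaluable, 10% loss and 270 enrolled is true as written. It also matters how far the attained power lies from the stated 80%, since a reader will take the three figures together.

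**Working it through.** **Inputs.** All come from Sample size {14}, except where noted: difference 0.5; SD 1.40; power 80%; alpha 0.05; required number 123 per group; loss 10% (repeated as a maximum in {20c}); enrolled 135 per group; total 270 (abstract). Sidedness is not stated. Two-sided is assumed because it reproduces 123; a one-sided calculation gives 97.

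**Step 1: reproduce the 123.** By the normal approximation,

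n per group = 2 × [(1.960 + 0.8416) × 1.40 / 0.5]² = 123.07.

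The stated 123 is reproduced.

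**Step 2: find where the 135 comes from.**

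- 123 × 1.10 = 135.3, which matches the stated 135.
- 123 / 0.90 = 136.7, so 137 per group and 274 in total. This is the number that leaves 123 after a 10% loss.
- Difference: 2 per group, 4 in total.

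**Step 3: what 135 leaves.**

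- At 10% loss: 135 × 0.90 = 121.5, that is 121 or 122 per group, 1 to 2 below 123. In total, 270 × 0.90 = 243 against 2 × 123 = 246.
- Largest loss that still leaves 123: 135 − 123 = 12, and 12 / 135 = 8.9%.

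Steps 2 and 3 use only 123, 10% and 135, so they do not depend on the test or on sidedness.

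**Step 4: power at these numbers** (difference 0.5, SD 1.40, two-sided 0.05).

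| Evaluable per group | Normal approximation | Exact t-test |
|---|---|---|
| 121 | 79.3% | 79.0% |
| 122 | 79.7% | 79.3% |
| 123 | 79.98% | 79.7% |
| 135 (no loss) | 83.5% | 83.2% |

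Relative to 123 per group, a full 10% loss costs about 0.3 to 0.7 percentage points by either method.

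**The case against.** The strongest case against the point is that it is immaterial, and on size that is right. The shortfall is 1 to 2 children per group and less than 1 point of power. It is also smaller than the precision of the inputs: with an SD of 1.39 instead of 1.40, the formula in Step 1 gives 121.3, so a change of 0.01 in the assumed SD covers the whole gap. The shortfall arises only near the top of the anticipated range. Section {20c} expects few withdrawals, all data are collected in a single visit, and randomisation follows consent and the first questionnaire, shortly before the procedure. Up to 8.9% loss, the required 123 is still met. All of this stands and sets the grade at minor. It does not make the sentence correct, because the plan names 10% and 135 does not cover 10%.

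Three stronger readings are tempting, and the document does not support them.

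- *The trial is underpowered.* A reader might infer this from 135 falling short of 137. Power of about 79% in the worst anticipated case, and about 83% with no loss, does not bear it out.
- *The base figure of 123 is itself wrong, so the enrolment target is further off.* The normal formula gives 123.07 and the exact t-test 124.04, so a reader might start from a higher base. The protocol does not name its formula, and 123 gives 79.98% power under the one that reproduces it. Adding a choice of formula to the dropout slip would only enlarge the apparent gap.
- *A baseline-adjusted primary analysis would make up the difference.* Section {20a} plans an unadjusted independent t-test or a Mann-Whitney U test, and the protocol gives no correlation between the scores before and after the procedure. No such rescue can be claimed from this document.

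**Conclusion.** The point holds as a minor arithmetic error. The stated allowance for a 10% loss in fact covers 8.9%; a full 10% would take 137 per group (274) rather than 135 (270). At the maximum anticipated loss, 121 to 122 complete cases per group remain and t-test power is 79.0% to 79.3%, against 79.7% at 123 and the stated 80%. No estimate, test or conclusion of the trial is affected.

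The enrolment arithmetic rests on no assumption beyond the plan's own three figures. The power figures assume two-sided 0.05, the planning difference and SD as stated, and the t-test. They do not carry over exactly to the Mann-Whitney alternative.

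**What to change.** Restate the last sentence of Sample size {14} so that its figures agree, for example: *We will include 135 children per group (270 in total). This keeps the required 123 evaluable per group with a loss of up to 8.9% (12 of 135); at a loss of 10%, t-test power is about 79% (two-sided alpha 0.05).* If the sponsor confirms that alpha is two-sided, that should be stated there too. The 10% maximum in {20c} can then stand, as long as it is no longer presented as fully covered by the 135.

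The cost is one sentence and a slightly less favourable dropout or power figure. Enrolment need not change: the 2 extra children per group would recover less than 1 point of power, and only at the maximum loss. The restatement should be justified by that small size and not by any adjusted analysis.

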### Recruitment {15}

To help the recruitment and preliminary inform the patients, posters will be put up in the emergency room and the patients will receive a flyer from the physician at the emergency room.

### Assignment of interventions: allocation

#### Sequence generation {16a}

Participants will be randomly assigned to the control or the intervention group with a 1:1 allocation. The randomisation schedule is computer-generated (in Castor Electronic Data Capturing System) and is stratified by age group (ages 5–11 and 12–17) using blocks of random sizes. The block sizes are computer-generated and therefore not known by the investigator. A stratified randomisation is used to ensure that the two groups have a similar distribution in age as this parameter may affect the outcomes [3].

#### Concealment mechanism {16b}

The randomisation is done in Castor EDC. Each patient is randomised after the investigator receives the completed written informed consent forms from the child and/or parent/guardian present and after the first questionnaire is completed. Therefore, the randomisation allocation is not revealed until the patient is included in the study to ensure the allocation group has no effect on the participant’s decision.

#### Implementation {16c}

The allocation sequence will be automatically generated by Castor EDC and is unknown to the investigator. The patients will be enrolled by the investigator, and the randomisation is also initiated by the investigator. The participants will be randomly assigned to the intervention or control group.

### Assignment of interventions: blinding

#### Who will be blinded {17a}

No one is blinded in this study.

#### Procedure for unblinding if needed {17b}

Not applicable.

### Data collection and management

#### Plans for assessment and collection of outcomes {18a}

The following demographics of the patient are collected from the patient’s medical records: date of fracture, date of plaster intervention, age, sex, upper or lower extremity fracture, specific location of the fracture, type of plaster treatment (plaster replacement or removal) and previous experiences with plaster removal. After randomisation, additional demographic data is collected from the patient or accompanying parent/guardian and the orthopaedic practitioner before the plaster intervention (e.g. the use of pain killers, method of plaster removal (if applicable) and the video chosen (if assigned to the intervention group)).

Additionally, data is collected with short questionnaires before and after the procedure. The child’s anxiety and pain scores are collected before and after the procedure, using the Child Fear Scale [15] (CFS) and the Numeric Rating Scale (NRS pain), respectively. The child’s and parent’s satisfaction will be collected after the procedure using the NRS satisfaction.

Lastly, the child’s fastest heart rate (during the procedure) is collected with the finger pulse oximeter.

All data is collected by a single individual. The principal investigator will randomly check the data entry during the study.

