#### Intervention description {11a}

The investigational group will receive standard care and will wear the VR goggles and headphones as well as a finger pulse oximeter during the plaster procedure. The VR goggles will play a video during the procedure to distract the child. The headphones will make sure that the child is more focused on the video by playing the sound of the video and by drowning out the noise of the procedure.

The control group will receive standard care and will wear the finger pulse oximeter.

Each age group (5–11 and 12–17) will have a choice between two videos of approximately 20 min long. The video length is based on the maximum length of the plaster intervention. The children can choose between single episodes of different series on Netflix. The content of the video is based on Netflix recommendations and is screened to make sure the content is appropriate for the hospital setting and the age group.

Children between the ages of 5 and 11 years have a choice between Masha and the Bear season 1 episode 2 and The Thundermans season 1 episode 2; children aged 12–17 years can choose between Modern Family season 1 episode 2 and Brooklyn Nine-Nine season 1 episode 2.

Masha and the Bear is an animated series that focusses on the adventures of a little girl named Masha and a fatherly bear that keeps her safe and prevents disasters. The Thundermans is a comedy series that revolves around the Thundermans, a family with superpowers who try to live normal lives. The spoken language of both videos is set to Dutch.

Modern Family is a sitcom and follows the lives of three diverse families and is filmed from the perspective of an unseen documentary maker. Brooklyn Nine-Nine is a comedy series following the immature but talented NYPD detective Jake Peralta and his diverse, lovable colleagues as they police the NYPD’s 99th precinct. The spoken language of both videos is set to English with Dutch subtitles.

Before the procedure, the child’s anxiety and pain scores are collected with a short questionnaire, using the Child Fear Scale (CFS) [14] and the Numeric Rating Scale (NRS pain), respectively. Then, the orthopaedic practitioner explains the plaster procedure, the finger pulse oximeter is put on and the randomisation result is revealed.

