#### Relevant concomitant care permitted or prohibited during the trial {11d}

All concomitant care is permitted.

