### Methods for additional analyses (e.g. subgroup analyses) {20b}

Descriptive statistics will be provided on the baseline demographic data.

Subgroup analyses will be performed, based on age (5–11 and 12–17), sex (female and male), type of plaster treatment (plaster removal and plaster replacement), method of plaster removal (saw and scissors compared to scissors only), the extremity fractured (upper and lower extremity), the specific location of the fracture (three most frequently found fractures in this study, presumably: distal radius, hand and distal humerus) [16], the use of painkillers and previous experiences with plaster removal.

The statistical package SPSS (version 25, IBM Corp, Armonk, NY, USA) will be used for all statistical analyses.

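### Two subgroup factors, painkiller use and method of plaster removal, are recorded after the allocation is known, so membership of those subgroups could depend on the arm

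*Protocol article*

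**What the plan says.** The order of events is set out in several places in the protocol article.

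- Intervention description {11a}: the child first gives anxiety and pain scores and the practitioner explains the procedure. Then "the finger pulse oximeter is put on and the randomisation result is revealed".
- Plans for assessment and collection of outcomes {18a}, and in near-identical terms Outcomes {12}: "After randomisation, additional demographic data is collected from the patient or accompanying parent/guardian and the orthopaedic practitioner before the plaster intervention". The examples given are "the use of pain killers, method of plaster removal (if applicable) and the video chosen (if assigned to the intervention group". Video choice exists in one arm only, so whoever completes this step knows the arm.
- Who will be blinded {17a}: "No one is blinded in this study".
- {18a} also states: "All data is collected by a single individual".
- Relevant concomitant care {11d}: "All concomitant care is permitted".
- Methods for additional analyses {20b} lists among the subgroup factors "method of plaster removal (saw and scissors compared to scissors only") and "the use of painkillers and previous experiences with plaster removal". It sets no condition that a factor be fixed or recorded before allocation.

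The remaining six factors in {20b} are age, sex, type of plaster treatment, extremity, fracture location and previous experience of removal. {12} and {18a} take all six from the medical record, outside the post-randomisation step.

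**The concern.** A comparison of arms within a subgroup has the protection of randomisation only if the arm cannot influence who is in the subgroup. For six of the eight factors the stated source makes that safe. For these two, the value is supplied by people who know the arm and is entered by a collector who knows it.

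The two routes differ in strength. The practitioner who reports the removal method also carries it out. Knowing that a frightened child will or will not wear goggles, the practitioner could choose or describe the method differently. Painkillers may well have been taken before arrival, so the main route there is a different answer, or a different recording of it, once the arm is known. The time of intake is not defined.

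If membership did shift with the arm, the two levels of the factor could show opposite false effects. That would look like a VR effect that depends on how the plaster is removed.

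**Working it through.** The plan gives no figure for this point, so the check has two parts: the sequence of events, and the size of bias that the sequence would allow.

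**Sequence.** (1) First questionnaire and practitioner's explanation. (2) Allocation revealed. (3) Painkillers, removal method and video recorded. (4) Plaster procedure. (5) Post-procedure scores. Step 3 follows step 2, so knowledge of the arm can act on the entries. Step 3 precedes steps 4 and 5, so neither the procedure nor the outcome scores can.

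**Inputs from the protocol** (Sample size {14}): SD 1.40, target difference 0.5, 123 analysed per group. The 123 reproduces with two-sided alpha 0.05 (sidedness is not stated) and 80% power: 2 × (1.40 × (1.960 + 0.842) / 0.5)² = 123.07.

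**Illustration A. Assumptions not in the documents:** no true effect; 30% of children are scissors-only; in controls alone, the most anxious sixth has a scissors-only share raised by δ; pre-procedure anxiety *z* correlates *r* with the outcome.

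- Mean *z* in the top sixth of a standard normal is 1.50, and in the rest −0.30.
- Among scissors-only controls, mean *z* = (1/6 × 1.50 × δ) / (0.30 + δ/6) = 0.25δ / (0.30 + δ/6).
- Among saw controls, mean *z* = −0.25δ / (0.70 − δ/6).
- In the VR arm both means are 0. The false VR effect is minus the control mean *z*, times *r* × 1.40.

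| δ | *r* | False effect, scissors only | False effect, saw |
|---|---|---|---|
| 0 | any | 0 | 0 |
| 0.10 (saw 60%) | 0.4 | −0.079 × 0.56 = −0.04 | +0.037 × 0.56 = +0.02 |
| 0.10 (saw 60%) | 0.7 | −0.079 × 0.98 = −0.08 | +0.037 × 0.98 = +0.04 |
| 0.30 (saw 40%) | 0.7 | −0.214 × 0.98 = −0.21 | +0.115 × 0.98 = +0.11 |

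A simulation of the last row with 400,000 children gave −0.216 and +0.104, which agrees closely.

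**Illustration B. A different model, also assumed:** half the children are scissors-only, fear determines the outcome fully (the equivalent of *r* = 1), and in controls alone the log-odds of scissors-only rise with fear. Simulated with 2,000,000 children and no true effect:

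| Log-odds slope per SD of fear | Scissors only | Saw | Difference between subgroups | Overall |
|---|---|---|---|---|
| 0 | 0.002 | −0.001 | 0.003 | 0.000 |
| 0.25 | −0.170 | +0.175 | −0.345 | 0.002 |
| 0.5 | −0.328 | +0.327 | −0.655 | −0.001 |
| 1.0 | −0.577 | +0.580 | −1.156 | 0.001 |

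The overall comparison stays at zero in every row. If the method depended on fear equally in both arms, the shifts would cancel; it is dependence on the arm that does the damage. If practitioners leaned the other way, the signs would reverse.

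**The case against.** The time of recording is not the time at which a fact is settled. The practitioner explains the procedure before the allocation is revealed. If the method is fixed by then, the later entry merely copies a pre-allocation fact. The painkiller window is a short interval within one visit, and no particular reason appears why a parent would answer differently by arm. The inputs to the illustrations are assumed. With about 0.30 × 123 = 37 scissors-only children per arm, the standard error of the difference is 1.40 × √(2/37) = 0.33, larger than the 0.21 bias in Illustration A.

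Much of this stands, and it limits what can be claimed. A reader might infer any of four stronger things that the documents do not support:

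- That subgroup membership does depend on the arm. The text shows only that it could; it does not say when the method is decided.
- That the plan declares these two factors to be baseline. {12} and {18a} call them demographic, but {20b} uses the word baseline only for the descriptive statistics and does not apply it to the subgroup factors.
- That the trial's main result is at risk. It is not, and the only subgroup with a stated hypothesis is age, which is a randomisation stratum.
- That painkillers are as exposed as removal method. That route is weaker, and neither illustration covers it.

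The objection does not remove the point. Nothing in the protocol establishes that the method is settled before allocation, so the data could not tell a real difference between subgroups from selection by arm. Sampling noise is no defence either, because a confidence interval does not include this bias.

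**Conclusion.** The point holds in a limited form. Two of the eight planned subgroup factors are recorded with the arm known, and membership could depend on it, mainly for removal method. Under assumptions that the documents neither confirm nor exclude, the false effect in the scissors-only subgroup is 0 if the choice of method does not depend on fear. It is about 0.04 to 0.22 CFS points under modest dependence in controls, and about 0.6 under strong dependence. Against the 0.5-point target, the modest range is 8% to 44% (0.04/0.5 and 0.22/0.5), and the strong case exceeds the target. The upper figure needs both strong dependence on fear in one arm only and an outcome fully determined by fear, so it is a bound for illustration, not an expectation. The overall primary and secondary comparisons and the other six subgroup factors are unaffected. The change is worth making because it is cheap, not because harm has been shown.

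**What to change.** For children still to be enrolled:

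- Add painkillers already taken to the first questionnaire.
- Have the practitioner's intended removal method entered in Castor when the procedure is explained, before the allocation is revealed.
- Define both subgroups in {20b} from these entries.
- Record the method actually used as a separate field and report it by arm descriptively only.

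This changes when data are written down, not how the plaster is removed; the practitioner remains free to depart from the stated intention.

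For children enrolled under the present order (recruitment began on 21 January 2021), label the two subgroup results as based on post-randomisation data and interpret them as descriptive only. If enrolment is complete, this labelling is the whole remedy.

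The cost is two case report form fields moved or added and a short amendment. Intended and actual method may differ in a few children. The two subgroup datasets will also be mixed across the date of change, so the pre-allocation entries will cover only part of the sample.

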#### Plans to promote participant retention and complete follow-up {18b}

Not applicable.

#### Data management {19}

The data is coded by the coordinating investigator of the study. Every patient will be given a consecutive alphanumeric code, consisting of the letters “VR” and three numbers, which will be used for data collection. All data is entered electronically in Castor EDC where all changes to the data will be documented in an audit trail. Only the investigators involved in this study can access and edit the data.

All forms collected for this study, including the signed consent forms, will be stored in locked file cabinets at the research secretariat and will be kept there for 15 years after the completion of the study.

